### Safety

An independent data and safety monitoring committee (DSMC), comprising experts in clinical trials, biostatistics, neurosurgery and intensive care medicine, was established before patient enrolment to review all trial protocols. The DSMC will assess the differential cumulative ‘SAE’ reports received after every 100 patients enrolled. In addition, after enrolling 430 patients (half of total recruitment), recruitment data, all safety-related data and outcome data will be reviewed by the DSMC in an un-blinded fashion. Consistent with previous literature,^20^ adverse events already defined and reported as study outcomes are not labelled and reported a second time as SAEs. The DSMC can, in its absolute discretion, request assessment of any other trial data at any time.

It is recognised that the study patient population will experience several common abnormalities in symptoms and clinical presentation due to the severity of the underlying disease and the impact of standard therapies. These do not necessarily constitute an adverse event unless they are directly related to study interventions, require significant intervention or are of concern in the investigator’s clinical judgement.

A SAE is defined as any adverse event that: results in death, is life-threatening, requires hospitalisation or prolongation of current hospitalisation, results in persistent or significant disability or incapacity, or is an important medical event which requires intervention to prevent one of the previously listed outcomes. For a list of predefined adverse clinical events, please refer to the online supplemental material.

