## Methods and analysis

### Trial design

BONANZA-GT is an international, multicentre, two-arm, open-label, randomised controlled trial of early PbtO_2_ monitoring and optimisation in patients with sTBI. This trial has been registered with the Australian and New Zealand Clinical Trials Registry (ACTRN 12619001328167). Recruitment commenced on the 13 January 2020 and is expected to be completed by December 2028.

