#### Phase I

At trial commencement, each new participating site has the option of completing a *run-in phase* if permissible under local ethics regulations. This involves the enrolment of up to four non-randomised patients, all of whom receive PbtO_2_ probes and are managed according to the PbtO_2_/ICP optimisation algorithm. This phase allows sites to resolve any unforeseen logistical, technical or clinical issues with the PbtO_2_ probe and the PbtO_2_ optimisation algorithm. These patients are additional and will not be included in the primary analysis, although they do contribute safety data.

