#### Phase II

To demonstrate separation in PbtO_2_ values between the two groups, all patients (control and intervention arms) had both PbtO_2_ and ICP catheters inserted and secured via a dual channel Licox PMO bolt (Integra LifeSciences, Plainsboro, NJ, USA) or other locally approved techniques. Randomisation occurred post-procedure. Following randomisation and device calibration, bedside clinical staff were blinded to PbtO_2_ values in control patients with the placement of a locked cover over the Licox monitor. Patients allocated to the intervention arm were treated according to the integrated BONANZA-GT PbtO_2_/ICP optimisation algorithm (figure 2). Patients allocated to the control arm received standard care (according to ICP-based interventions alone, figure 3). Control group PbtO_2_ values were only accessible to unblinded study coordinators for periodic checks of appropriate probe response. Enrolment into phase I was completed on 15 December 2023 following the conclusion of a planned treatment separation analysis. The findings from phase II will be reported separately.

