#### Phase III

Patients enrolled into phase III will be randomised to either standard care (ICP-only-guided management) or integrated PbtO_2_/ICP optimisation, prior to device insertion. Patients randomised to the intervention arm will have ICP and PbtO_2_ monitoring devices inserted as per local practice; no PbtO_2_ catheter will be inserted in control patients. Patients allocated to the intervention arm will be treated according to the integrated BONANZA-GT PbtO_2_/ICP optimisation algorithm (figure 2). Patients randomised to the control arm will be treated according to the ICP/CPP optimisation algorithm (figure 3). Placement of intracranial monitoring devices must occur as early as possible after randomisation.

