### Study outcome measures

Details of all outcome measures are listed in Box 3.

Box 3Brain Oxygen Neuromonitoring in Australia and New Zealand Assessment – Global Trial primary and secondary outcome measuresPrimary outcome measureProportion of favourable neurological outcomes (GOS-E: 5–8) at 6 months following injury.Secondary outcome measuresProbability of an equal or greater GOS-E level at 6 months compared with the probability of a lesser GOS-E level using a proportional odd model.Probability of an equal or greater GOS-E level at 6 months compared with the probability of a lesser GOS-E level using the ‘sliding dichotomy’ method.EQ-5D-5L at 6-month and 12-month post-injury.Proportion of favourable (GOS-E: 5–8) neurological outcomes at 12 months following injury.Mortality (all cause) at intensive care unit discharge, hospital discharge, and 90-days and 180-days post-injury.Incidence of adverse events.GOS-E, Glasgow Outcome Scale-Extended.

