### Risks associated with treatment algorithm

Treatment of ICP elevations in the BONANZA-GT protocol is based on widely accepted management protocols. The available evidence indicates that the risks of these interventions are outweighed by the potential for decreased ICP-related mortality and morbidity.^4 19^ Participants who are randomised to the ICP-only treatment arm will not be subject to any risks over and above those associated with standard care. Participants randomised to PbtO_2_-guided management may be exposed to the risk of specific treatment-related complications from interventions such as fluid boluses or vasopressors to increase CPP,^27^ transfusion of packed red blood cells^28^ and ventilator adjustments.^29^ It is important to note that these interventions are effective at reversing cerebral hypoxia and are not associated with significant adverse events in prior literature (including the recent OXY-TC trial). In addition, all these interventions are commonly provided in the setting of acute trauma resuscitation and management. More specifically, recently published trials support a liberal red blood cell transfusion strategy in sTBI patients,^30 31^ and it is possible BONANZA-GT may provide supporting evidence as to physiological mechanisms underlying the beneficial effects observed in these studies.

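### In an open-label trial, the rule for counting common abnormalities as adverse events turns partly on attribution and investigator concern, which leaves the between-arm adverse-event comparison open to differential ascertainment

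*Protocol article*

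**What the plan says.** All references are to the protocol article.

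- **Counting rule (Safety).** Patients with this injury are expected to show several common abnormalities caused by disease severity and standard therapy. Of these the article says: "These do not necessarily constitute an adverse event unless they are directly related to study interventions, require significant intervention or are of concern". The sentence ends by tying the last trigger to a person: such events count if they "are of concern in the investigator’s clinical judgement".
- **Use of the count (Study outcome measures, Box 3).** "Incidence of adverse events" is a secondary outcome. Under Safety, the monitoring committee also assesses differential cumulative reports of serious adverse events after every 100 patients, and a serious event is defined there as an adverse event that meets a seriousness criterion.
- **Knowledge of allocation.** Trial design describes an "international, multicentre, two-arm, open-label, randomised controlled trial". In phase II, "bedside clinical staff were blinded to PbtO_2_ values in control patients with the placement of a locked cover over the Licox monitor". In phase III, "no PbtO_2_ catheter will be inserted in control patients". Randomisation and blinding states blinded central assessment for the 6- and 12-month follow-up outcomes and does not mention adverse events.
- **Where the extra risk lies (Risks associated with treatment algorithm).** Participants under PbtO2-"guided management may be exposed to the risk of specific treatment-related complications" from fluids or vasopressors, transfusion and ventilator changes. Control participants are said to face no risk beyond standard care.
- **Predefined list (Safety).** A list of predefined adverse clinical events is placed in the online supplement, which is not shown.

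**The concern.** A between-arm comparison of event incidence estimates harm only if an event of a given kind has the same chance of being counted in either arm. Here, part of the rule asks whether an abnormality was caused by the study interventions, and another part asks whether the investigator is concerned about it. Both questions are answered by people who are not stated to be blinded.

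The first question also has a different scope in the two arms. A complication following a fluid bolus given for low brain tissue oxygen can be attributed to the study intervention. The same complication following a bolus given as usual care in a control patient has less of a route through that trigger.

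What is at stake is the safety conclusion. The article itself, under Risk of intracranial monitoring, cites an earlier trial with intracerebral haematoma in 4% of the combined-monitoring group against 0% of the group monitored for intracranial pressure only. Harm will therefore weigh in how the result is read. Attribution-dependent counting could inflate apparent harm, or hide it if complications are set aside as expected in such patients.

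**Working it through.** The article gives no adverse-event rate, no recording probability and no calculation for this outcome, so there is no figure to reproduce. Its only design calculation concerns the primary outcome and does not bear on this point. The check is a reading of the sections against each other.

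**Step 1. Is each trigger symmetric between arms?**

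| Trigger | Intervention arm | Control arm |
|---|---|---|
| Attributed to study interventions | Covers oxygen-driven treatment and the probe | No oxygen-driven treatment. Probe present in phase II, absent in phase III. The pressure-based algorithm could be read as a study intervention |
| Needs significant intervention | Available | Available |
| Of concern to the investigator | Available, judged with no stated blinding | Available, judged with no stated blinding |

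Even on the generous reading, in which the pressure-based algorithm counts as a study intervention in both arms, the oxygen-driven component remains on one side only. The first trigger is asymmetric in scope. The third has equal scope but is open to knowledge of allocation. The second depends on need and is formally open to both arms.

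**Step 2. Do those applying the rule know the allocation?** In phase III the presence or absence of the oxygen catheter shows it. In phase II the stated blinding covers the oxygen values of control patients, not the allocation. No blinded adjudication of adverse events is stated for either phase.

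**Step 3. Does the rule feed a comparison?** It does in two places. One is the secondary outcome in Box 3. The other is the committee's differential reports, because a serious event must first be an adverse event. The second route is probably the less exposed: an abnormality serious enough to qualify will often need significant intervention and so pass the gate in either arm.

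**Step 4. Can the size be obtained?** Let p_I and p_C be the true event probabilities in the intervention and control arms, and r_I and r_C the probabilities that a true event is counted. Then

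apparent risk ratio = (p_I × r_I) / (p_C × r_C) = true risk ratio × (r_I / r_C).

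The distortion is the factor r_I / r_C. If recording is equal, the factor is 1 and there is no distortion. It exceeds 1 if attribution adds events in the intervention arm, and falls below 1 if complications there are dismissed as expected. The article gives nothing from which r_I or r_C could be set, so both direction and size stay undetermined.

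**The case against.** The strongest reply has four parts.

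1. **The rule is softer than it may look.** It says such abnormalities do not necessarily count, it covers only those common in this population, and investigator judgement most naturally attaches to the concern trigger alone. The triggers are alternatives, and need for significant intervention applies to both arms. This stands. It confines the problem to events that enter only through relatedness or concern.
2. **A predefined list exists and may already fix what is recorded.** This also stands, and it limits confidence. However, the main text does not say that the list overrides the rule, or that listed events are recorded regardless of attribution.
3. **The main conclusions are protected.** Six-month outcome is assessed by blinded central assessors, all-cause mortality does not depend on this rule, and an independent committee reviews all safety data unblinded at 430 patients and may request other data. This is correct and limits the consequence to the adverse-event comparison. Committee review does not restore events that were never recorded.
4. **An article condenses the full protocol.** That is so, but the counting rule is printed here, and the point rests on what it says.

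A reader might also infer that the run-in patients distort the comparison, since Phase I says of them: "although they do contribute safety data". The documents do not support that. Contributing safety data is not the same as being pooled with an arm, and nothing says they are pooled. Statistical analyses bases the analysis of patient outcomes on randomly assigned patients, and the run-in patients are not randomised.

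**Conclusion.** The point holds as a risk of differential ascertainment. As written, a common abnormality can become an adverse event through attribution to interventions that differ between arms, or through the concern of an investigator who is not stated to be blinded. The secondary adverse-event outcome and, probably to a lesser degree, the differential serious-event reports are exposed.

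A reader might go further and conclude that the comparison is biased, or that events count only when unblinded staff say so. Neither follows. The first needs a recording ratio that the documents do not give. The second overlooks the softer wording of the rule, the need-based trigger and the predefined list.

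The conclusion assumes that the supplement does not already require the listed events to be recorded in both arms regardless of attribution. If it does, the remaining task is to say so in the main text. Confidence is medium for that reason. The primary outcome and mortality are unaffected.

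**What to change.** Define the between-arm adverse-event outcome as the predefined clinical events already listed in the supplement, recorded in both arms by the same criteria whatever the suspected cause. Keep relatedness and investigator concern as separate fields, used only for descriptive and regulatory reporting. Apply the same separation to the differential reports for the monitoring committee. State in the Safety section that the rule on common abnormalities does not govern the listed events.

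Recruitment began in January 2020, so it should also be checked how the listed events were recorded in patients already enrolled, and any change in recording should be reported by phase.

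The cost is a change of wording in the protocol and the case report form guidance, and slightly more event recording in control patients. The randomisation, sample size and primary analysis do not change.

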### Statistical analyses

The proportion of participants in the control group with a favourable outcome (Glasgow Outcome Score-Extended (GOS-E) >4) at 6 months in the Decompressive Craniectomy in Diffuse Traumatic Brain Injury study was 49%.^21^ In the Erythropoietin in Traumatic Brain Injury study, in those with a severe head injury (GCS 3–8), 50% of patients in the control arm had a favourable outcome.^22^ We considered a clinically relevant effect size to be 10% absolute (20% relative) increase in favourable outcomes (a conservative estimate, given the OR for a favourable outcome was 1.8 in BOOST-2^17^). As such, with a control event rate of 50%, with 80% power, and a two-sided α of 0.05, a sample size of 816 patients is required. Based on a combined withdrawal and loss to follow-up rate of 5%, consistent with previous trials, we have inflated the sample size to 860 patients (430 in each group).

We prespecified 10% absolute improvement in favourable GOS-E at 6 months as clinically important. With an expected control rate of 50%, this equates to a number-needed-to-treat of 10, which reflects a meaningful gain in independent survival for patients and families. This threshold is consistent with absolute differences commonly targeted in phase III TBI trials. Furthermore, to quantify smaller distributional shifts in outcome, secondary analysis will be performed using GOS-E as an ordinal outcome.

Randomised patients from phases I and II are pooled for the primary efficacy analysis; run-in patients are non-randomised and excluded. The primary analysis will use a covariate-adjusted model, including site and covariates known to impact outcome, thus improving precision in the presence of between-patient and between-site heterogeneity. Analysis of patient outcomes will use an intention-to-treat principle and include all randomly assigned patients except those withdrawing consent for use of all trial data. Prior to the enrolment of the last patient, a detailed statistical analysis plan will be published separately.

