### Risk of intracranial monitoring

Intracranial neuromonitoring involves an invasive procedure that is not risk-free. Current literature indicates a rate of probe-associated bleeding between 2.6% and 11%^24^,^26^ and the OXY-TC trial found a small but significant increase in the rate of intracerebral haematoma in the ICP/PbtO_2_ group (4%), compared with the ICP-only group (0%).^18^ BONANZA-GT aims to minimise patient risk by recruiting only patients with a clearly documented requirement for intracranial monitoring which is independent of trial inclusion. Phase III of BONANZA-GT now only requires PbtO_2_ catheter placement in patients allocated to the intervention arm and avoids any potential unnecessary risk of PbtO_2_ probe-related complications in control patients. All study devices must be inserted by trained neurosurgical staff and monitored carefully for any associated adverse events. The BONANZA-GT DSMC will assess all device-related adverse events and provide independent advice regarding any safety signal.

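### Pooling phases II and III shrinks the between-arm comparison of probe harm and makes the efficacy estimate a mix of two contrasts; compare device events in phase III only and report effects by phase

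*Protocol article*

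**What the plan says.** **Phase II.** All patients in both arms had oxygen and pressure catheters placed, and "Randomisation occurred post-procedure". Control readings were hidden under a locked cover.

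**Phase III.** Randomisation now precedes insertion, and no oxygen "catheter will be inserted in control patients".

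**Pooling.** Randomisation and blinding places every phase II and phase III patient in the primary intention-to-treat analysis. Statistical analyses also pools, but names phases I and II, although the section Phase I describes a non-randomised run-in that stays out of the primary analysis. The same paragraph states that patient outcomes are analysed by intention to treat in all randomised patients, apart from those who withdraw consent for use of all their data. Box 3 lists incidence of adverse events among the secondary outcomes.

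**Model.** "The primary analysis will use a covariate-adjusted model, including site and covariates known to impact outcome". Phase is not named, and randomisation is stratified by site only.

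**Probe harm.** Risk of intracranial monitoring gives probe-associated bleeding of 2.6% to 11% and says the cited phase III trial "found a small but significant increase in the rate of intracerebral haematoma": 4% with the probe and 0% without. It adds that the phase III design spares controls this risk.

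**Control-arm risk.** Risks associated with treatment algorithm says: "Participants who are randomised to the ICP-only treatment arm will not be subject to any risks over and above those associated with standard care".

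**The concern.** Phase II asks whether acting on oxygen readings helps when every patient already carries a probe. Phase III asks whether the whole strategy helps, including the harm of the probe and the patients in whom placement fails or is delayed. The stated objective, oxygen-guided care in addition to pressure targets against pressure-guided care alone, matches the phase III contrast. The article does not say that the comparison changed.

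Two things follow.

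- Phase II controls carry the same probe risk as phase II intervention patients, so probe bleeding cancels between arms in that phase. A comparison over all randomised patients is pulled towards no difference on the harm that the article itself singles out and that prompted the change of design. The data and safety monitoring committee's review of differential serious adverse events, every 100 patients, is affected in the same way if its tables combine the phases.
- The pooled efficacy estimate is an average weighted by enrolment in each phase. If the probe costs any favourable outcomes, it shows the strategy as better than phase III alone would.

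**Working it through.** **1. The plan's own figure.** Inputs from Statistical analyses: "with a control event rate of 50"%, a "10% absolute (20% relative) increase in favourable outcomes", and "with 80% power, and a two-sided α of 0.05, a sample size of 816 patients is required".

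- Uncorrected: n = [1.96·√(2×0.55×0.45) + 0.8416·√(0.5×0.5 + 0.6×0.4)]² / 0.1² = 387.3, so 388 per arm (776 in total).
- With continuity correction: (387.3/4)·[1 + √(1 + 4/(387.3×0.1))]² = 407.1, so 408 per arm, or **816**, as stated.
- 816/0.95 = 859; the plan has 860.

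The sample size is sound on its inputs and is not at issue.

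**2. The phase II share, f.** The article does not give it. Recruitment began on 13 January 2020, and enrolment into the first randomised phase appears to have ended on 15 December 2023 (the sentence is in Phase II but says phase I). Completion is expected by December 2028. Even accrual would give f = 1,432/3,275 days = 0.44. This is an assumption: countries that joined late would make later accrual faster and f smaller. I therefore show 0.2 to 0.75.

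**3. Dilution of probe harm.** Let h be the probe event rate and take a rate of 0% without a probe, as in the cited trial.

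- Intervention arm, both phases: h.
- Control arm, pooled: f×h + (1−f)×0 = f×h.
- Pooled difference: (1−f)×h.

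Exact power of Fisher's test at two-sided 0.05 with h = 4%, using 430 per arm pooled and 430×(1−f) per arm in phase III:

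| f | Pooled difference (points) | Power, pooled | Phase III per arm | Power, phase III only (4% vs 0%) |
|---|---|---|---|---|
| 0.20 | 3.2 | 86% | 344 | 99% |
| 0.25 | 3.0 | 79% | 322 | 99% |
| 0.40 | 2.4 | 51% | 258 | 95% |
| 0.44 | 2.2 | 44% | 241 | 92% |
| 0.50 | 2.0 | 34% | 215 | 86% |
| 0.60 | 1.6 | 21% | 172 | 69% |
| 0.75 | 1.0 | 9% | 108 | 26% |

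The smaller comparison wins throughout for a simple reason. With N per arm and roughly equal variances, the pooled test statistic grows as (1−f)·h·√N and the phase III statistic as h·√((1−f)·N). Their ratio is √(1−f), always below 1; at f=0.5 it is 0.71.

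**4. Efficacy estimate.** Suppose acting on the readings has effect d in both phases, and the probe lowers the favourable-outcome rate by c.

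- Phase II effect: d, because the cost falls on both arms.
- Phase III effect: d − c.
- Pooled effect: f×d + (1−f)×(d − c) = d − (1−f)×c.
- Pooled minus phase III: f×c.

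The article gives no value for c. If half of probe bleeds turned a favourable outcome unfavourable (assumption), then c = h/2. At f=0.44 the excess is 0.44×2.6×0.5 = 0.6 points to 0.44×11×0.5 = 2.4 points, against a target of 10. With about 50% favourable outcomes, that assumption means that nearly every patient who bled and would have done well loses the good outcome. The range is therefore close to an upper bound for that f.

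**5. What an interaction test can show.** The standard error of the pooled effect is √((0.25+0.24)/408) = 3.5 points. With f=0.5 the treatment-by-phase interaction has standard error √(2×0.49/204) = 6.9 points, so a difference of a few points between phases could not be confirmed.

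**The case against.** **Pooling is valid.** Patients are randomised concurrently within each phase, so combining the phases neither biases the test of no effect nor inflates type I error. This stands. A reader might infer that the primary test is compromised; the document does not support that. The point concerns what the estimate means and how the harm comparison is made.

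**The details belong to the analysis plan.** The article promises a separate plan, and covariates known to affect outcome could include phase. So the absence of a phase term, an interaction or by-phase tables is not an error in itself. What the article does fix is the pooling of two different contrasts.

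**No pooled safety test is stated.** The primary-analysis sentences concern efficacy, phase II findings are to be reported separately, and the monitoring committee will assess device-related events. But adverse events are a listed outcome, and the article analyses patient outcomes in all randomised patients. Separate reporting of phase II does not promise a phase III device comparison. This objection does not remove the concern.

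**The size is uncertain.** This stands. The phase II share is unknown; at f=0.2 the pooled comparison still has 86% power. The effect of a bleed on the primary outcome is also unknown.

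**The control-arm risk sentence is about treatment, not devices.** It sits under treatment-algorithm risks and uses the future tense, and the section before it implies that earlier controls had probes. It is a matter of wording, not evidence that the risk was concealed.

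**Conclusion.** The concern holds in a limited form. The pooled primary analysis can stay. A between-arm comparison of probe-related events over both phases is diluted to (1−f)×h, and phase III alone has more power at every share examined, with fewer patients. At h=4% versus 0%, the power lost by pooling runs from about 13 percentage points at f=0.2 to about 52 at f=0.5. At f=0.75 both comparisons are weak (9% and 26%). These figures rest on the cited haematoma rates and an assumed f.

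The pooled efficacy estimate mixes two contrasts and exceeds the phase III strategy effect by f times any probe cost. That cost is unknown, and 0.6 to 2.4 points at f=0.44 should be read as near the most it could be.

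It is tempting to treat the unnamed phase term as the defect, or to claim that it loses precision. Neither is supported. A phase main effect does not separate the two contrasts, and the article gives nothing from which a gain in precision could be calculated.

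**What to change.** Keep the pooled primary analysis, and add the following before the analysis plan is published:

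1. Make the between-arm comparison of device-related events (haemorrhage, infection) in phase III only. Report phase II as incidence per probe inserted.
2. Pre-specify the treatment effect on the primary outcome by phase, with a treatment-by-phase interaction, as a supporting analysis. State that its power is low, so that a non-significant interaction is not read as evidence that the phases agree.
3. Treat a phase main effect in the model as optional; it does not replace items 1 and 2.
4. Reconcile the phase labels. Statistical analyses pools phases I and II, against the sections Phase I and Randomisation and blinding. Phase II gives a completion date for phase I where the context points to phase II.
5. Limit the statement on control-arm risk to phase III.

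The cost is wording and one extra table. The device comparison uses fewer patients but has more power. Patient care does not change. With recruitment still under way and the analysis plan still to come, these choices can be made before results are known.
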